### 2.2. Participants

The study aims to recruit 140 adults with ongoing mental illness (mood and psychotic disorders), living in the community at the Gold Coast (expected *n* = 45) and in Sydney (expected *n* = 95). Participants will be care-coordination clients of PCCS, an NGO that has previously developed and implemented SP programs in Australia [33,34]. PCCS has a steady flow of new care-coordination clients (who are referred by their GP) and these will form the recruitment pool. Eligibility criteria include:

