## 7. Statistical Analysis

### 7.1. Sample Size Estimation

A priori power calculation is based on self-reported quality of life WHOQoL-Bref [56] with reference values for mean and standard deviation taken from Spinal Cord Injury Research Evidence [67] and methods from Rosner [68]. Assumptions include α = 0.05, β = 0.2, and power = 0.8 (80%). Calculations indicate a sample of 126 participants is required to detect a minimum effect of 0.5 units (SD = 19.4) between control and intervention conditions post-intervention. We aimed to recruit 140 participants to allow for an attrition rate of 11%, i.e., between the 7% median attrition rate of RCTs [69] and estimated 12.9% in mental illness research [70].

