## 8. Ethical Considerations

Ethics approval for this research has been granted by the Southern Cross University Human Ethics Committee (2020/133). Protocol variations will be submitted to HREC and notification to appropriate parties conducted according to HREC recommendations. Participants in this study have a mental illness and as such are a considered a vulnerable group. All staff involved in participant contact are experienced in dealing with mental illness. Recruitment processes will ensure participants have the capacity to provide informed consent. Additionally, ongoing participant capacity to consent will be monitored by Link Workers and study staff; lack of ability to consent will result in withdrawal and referral to appropriate services. Withdrawn participants will be given the option to exclude their data from analysis.

Participants’ welfare will also be ensured throughout the study via as-usual monitoring, assessment, and service referral from PCCS Link Workers; these referrals will be participant-specific and could include referral to a range of biopsychosocial services, such as psychological and psychiatric services (including medication review) or welfare services. This frequent contact with Link Workers will also aid in retention as arising issues that limit ability to participate (for example lack of transport) fall within the purview of the Link Worker role and can be addressed. Finally, the study design has inherent ethical advantages over RCTs or crossover designs, as all participants will have access to the intervention, and the intervention will not be removed over the course of the study [49].

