### 9.3. Concurrent Treatments

Over the course of the study, participants will receive ongoing assessment and referral from PCCS Link Workers which may include, for example, psychological services or medication review. This concurrent care has the potential to confound assessment of the impact of the Forest Therapy intervention. However, this regular assessment and referral will be ongoing over the course of the entire study, and thus the same for both control and intervention time periods, limiting the confounding of these treatments. Furthermore, the vulnerable nature of participants with mental illness, and the length of the study (at least 25 weeks for each participant), requires consideration of the ethics and risk of withholding other treatments. Similarly, the translational nature of this research and the study sample (vulnerable participants accessing care services in the community) limits the capacity to control a variety of variables, including access to concurrent treatments.

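### A target of 140 covers 10% attrition from the required 126, not the 11% stated: a small arithmetic slip that wording can correct

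*Protocol article*

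**What the plan says.** All the figures stand in section 7.1 (Sample Size Estimation) of the protocol article. The calculation concludes that "a sample of 126 participants is required to detect a minimum effect of 0.5 units (SD = 19.4) between control and intervention conditions post-intervention". The recruitment target follows: "We aimed to recruit 140 participants to allow for an attrition rate of 11" per cent. The article explains the choice of 11% by placing it "between the 7% median attrition rate of RCTs [69] and estimated 12.9% in mental illness research [70"].

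Section 2.2 (Participants) repeats the target and describes who is enrolled: "The study aims to recruit 140 adults with ongoing mental illness (mood and psychotic disorders"). Section 8 (Ethical Considerations) describes a feature expected to limit losses: "This frequent contact with Link Workers will also aid in retention".

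**The concern.** An attrition rate is normally the share of enrolled participants who are lost. On that reading, a target that allows for 11% attrition should leave the required 126 after 11% of recruits have gone. It does not, so the article claims slightly more protection than 140 gives, and the error runs in the favourable direction.

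Little is at stake for the result. What matters is that a planning figure is stated incorrectly in an article whose Introduction lists sample size among the trial's improvements on earlier work. A reader who later compares actual losses with the stated allowance would use the wrong benchmark: losing 15 of 140 (10.7%) would look covered but would leave 125.

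**Working it through.** **Inputs (section 7.1):** required number 126; target 140; stated attrition 11%; cited benchmarks 7% and 12.9%; α = 0.05; power 80%. Sidedness is not stated, and two-sided is assumed below.

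**1. Reproducing the 140.**
- Adding 11% to the required number: 126 × (1 + 0.11) = 139.86, rounded up to 140. This is the printed target.
- Dividing by the share retained: 126 / (1 − 0.11) = 141.57, rounded up to 142.

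The printed figure matches the first form. That form measures the rate against those who remain, not those recruited: 14/126 = 11.1%, while 14/140 = 10.0%.

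**2. What 140 covers.** The largest loss that keeps 126 is 1 − 126/140 = 10.0%.

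**3. Expected number remaining, and recruits needed to keep 126.**

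| Attrition | Remaining of 140 | Recruits needed |
|---|---|---|
| 7% | 140 × 0.93 = 130.2 | 126/0.93 = 135.5, so 136 |
| 10% | 140 × 0.90 = 126.0 | 126/0.90 = 140 |
| 11% | 140 × 0.89 = 124.6 | 126/0.89 = 141.6, so 142 |
| 12.9% | 140 × 0.871 = 121.9 | 126/0.871 = 144.7, so 145 |

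The middle column counts every dropout as wholly lost to analysis.

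**4. Size in terms of power.** This needs a calculation that returns 126. Two equal, individually randomised groups with a standardised difference of 0.5, two-sided 5% and 80% power give

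n per group = 2 × (1.960 + 0.842)² / 0.5² = 62.8, so 63, and 126 in total.

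On that basis, power = Φ(0.5 × √(n/2) − 1.960), with n per group:
- 126 in total (n = 63): 80.1%
- 124.6 in total (n = 62.3): 79.7%
- 121.9 in total (n = 60.97): 78.8%

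The loss at 11% is 0.4 of a percentage point; at 12.9% it is 1.3 points.

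**5. Why these power figures are only a gauge.** The inputs as printed are a difference of 0.5 units with SD 19.4. Put in literally, they give 2 × (19.4/0.5)² × (1.960 + 0.842)² = 23,633 per group, not 63. The 126 follows only if 0.5 is read as 0.5 SD (0.5 × 19.4 = 9.7 units). That calculation makes no evident allowance for clustering or for the stepped-wedge design in section 2.1. This is a separate problem and is not resolved here.

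**The case against.** **The difference is immaterial.** It is two recruits in 142 (1.4%), and no decision on design, analysis or recruitment turns on it. This stands. It sets the weight of the point but does not make the sentence correct.

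**Dropout is not the same as loss from the analysis.** Each participant contributes control and intervention assessments, and the Analysis subsection plans a linear mixed model with repeated measures, which can use data from people who leave early. Section 8 offers withdrawn participants the choice of having their data excluded, which implies that data are otherwise kept. This also stands. The numbers remaining are therefore conditional on each dropout being wholly lost. The article nevertheless sets its own target as 126 plus a margin for attrition, and that margin is what is misstated.

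**A reader might infer that 11% is itself wrong**, because everyone enrolled has a mental illness and the article gives "estimated 12.9% in mental illness research [70"], and so that 12.9% must be the planning rate. The documents do not support this. The article openly places its rate between two cited figures, which contradicts nothing. The source of the 12.9% is not at hand, so its settings, diagnoses and length of follow-up cannot be matched to community clients followed by Link Workers. Section 8 also describes a retention measure that makes a somewhat lower rate defensible, although section 7.1 does not give it as the reason. On the other side, section 9.3 mentions "the length of the study (at least 25 weeks for each participant"), which is no ground for optimism but does not fix a rate either.

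**Conclusion.** The point holds as a minor arithmetic error. A target of 140 keeps 126 up to 10% attrition, not 11%; at 11% the expected number is 124.6, and 142 recruits would be needed. The likely cause is multiplying by 1.11 instead of dividing by 0.89. That is inferred from the match with the printed 140, since the article does not show the step.

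The finding rests on reading attrition as a share of those recruited and on counting each dropout as a full loss. The power effect also assumes the two-group 0.5 SD basis and a two-sided test.

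A reader might go further and conclude that the trial will end with fewer than 126. That does not follow: it is expected only if loss exceeds 10%, and at the 7% also cited about 130 would remain.

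**What to change.** Keep the target of 140 and change the wording of section 7.1 to say that it allows for 10% attrition from the required 126. Add that about 125 would be expected to remain at 11%, and about 122 at the cited 12.9%, if every dropout is wholly lost to analysis.

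Do not add a revised power figure at this stage. It would lend false precision to a base number that does not follow from the printed effect and SD. When the basis of the 126 is corrected, inflate the new number by dividing by one minus the attrition rate, so that the slip is not carried over.

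The cost is a sentence or two of text, with no extra participants and no change to design or analysis. If the sponsor prefers to keep the 11% statement, the consistent target is 142, at a cost of two more recruits.

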#### Analysis

Data will be entered, cleaned, checked, and analysed in SPSS 27 [71]. Within and between-group analysis will be conducted with differences considered significant at α = 0.05. Analysis will be conducted according to the methods of Hussey and Hughes [72] who have produced a guide to analysis for the (relatively new) stepped-wedge cluster design. A Linear Mixed Model (LMM) will be used as this allows for non-independence in the data including clustering and repeated measures. Weighted Least Squares (Weighted Linear Regression) will be used to estimate the fixed effects. Subgroup analysis will examine differences across mental illness diagnoses. Assessment tools missing <20% responses will be imputed with participant tool mean. Tools with >20 missing responses will be excluded.

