#### 5.2.2. Quality of Life

The World Health Organisation Brief assessment of QoL [56] assesses QoL over the previous 2 weeks. It is validated in adults with mental illness [57] and has good discriminant, content, and test-retest reliability [58]. Two overall items assess overall QoL and physical health, and four domains including social relationships, physical health, psychological health, and environment. Items are rated on a Likert scale from 1 (not at all/very poor) to 5 (completely/very good).

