## 6. Outcomes of interest

### 6.1. Primary Outcomes

Global Quality of Life—WHOQoL-Bref [56]Social Adjustment—Work and Social Adjustment Scale [59]Loneliness UCLA 3-item Loneliness Scale [60]

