#### 6.2.3. Physical Health

Physical Health Subscale of WHO-QoL-Bref [56]

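### Three unranked primary outcomes are each judged at 0.05 with no order, adjustment or success rule, and the primary WHOQoL-Bref score is not identified

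*Protocol article*

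**What the plan says.** Section 6.1 (Primary Outcomes) lists three outcomes side by side: Global Quality of Life on the WHOQoL-Bref, "Social Adjustment—Work and Social Adjustment Scale", and the UCLA 3-item Loneliness Scale. None is marked as first or main.

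The Analysis paragraph of section 7 gives one significance rule for everything: "Within and between-group analysis will be conducted with differences considered significant at α = 0.05". It then names a linear mixed model following a published guide to stepped-wedge analysis.

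Section 7.1 (Sample Size Estimation) covers one of the three outcomes: "A priori power calculation is based on self-reported quality of life WHOQoL-Bref". It uses α = 0.05 and 80% power, and arrives at 126 participants for an effect of 0.5 units with SD 19.4, raised to 140 for attrition.

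Section 5.2.2 describes the instrument behind the first primary outcome: "Two overall items assess overall QoL and physical health, and four domains including social relationships, physical health, psychological health, and environment". Section 6.2.3 places its physical health subscale among the secondary outcomes. No section says which score 'Global' refers to.

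Section 1.2 states the hypothesis as improvement relative to the control period. It does not say how many of the primary outcomes must improve.

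**The concern.** With three primary outcomes on equal footing and 0.05 for each, the natural reading is that significance on any of them may be reported as a positive primary result. The chance of at least one such result when the intervention does nothing is then above 5%, and nothing in the protocol limits it.

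This is a rule the protocol states and builds its sample size on, rather than a detail left open. If a later document split the 0.05 across the three outcomes, the stated 80% power would no longer hold at 126 participants.

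The unnamed WHOQoL-Bref score adds a second, smaller freedom. An overall item, a combination of the two overall items, or a total could each be called global quality of life after the data are seen. A reader also cannot tell whether the score that was powered is the score that will be tested.

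**Working it through.** **Inputs from the protocol article.** Three primary outcomes (6.1); 0.05 for each difference (Analysis); α = 0.05, power 0.80, N = 126, effect 0.5 units, SD 19.4 (7.1).

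**Assumptions.** Tests are two-sided, since sidedness is not stated. Any one significant primary outcome supports a claim. Correlations between the three test statistics are not given, so a range is shown.

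**1. The plan's own sample size.** For two equal groups, n per group = 2 × (1.960 + 0.842)² / d².
- With d = 0.5 SD: 2 × 7.849 / 0.25 = 62.8, so 63 per group and **126** in total. The stated figure is reproduced, as one two-sided test at 0.05.
- A one-sided test would give 100, which supports the two-sided reading.
- 126 follows from this formula only if the 0.5 is read in SD units (0.5 × 19.4 = 9.7 points). Read literally as 0.5 points with SD 19.4, the formula gives 23,633 per group.

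The whole 0.05 is therefore spent on one test of one score.

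**2. Chance of at least one false positive, three tests at 0.05.**
- Independent: 1 − 0.95³ = **14.3%**.
- Equally correlated normal test statistics with correlation r: 1 − ∫ φ(u) [Φ((1.96 − √r·u)/√(1−r)) − Φ((−1.96 − √r·u)/√(1−r))]³ du.
- Favourable direction only: drop the second Φ term. If independent, 1 − 0.975³ = 7.3%. The nominal rate for one test is 2.5%.

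| Correlation (assumed) | Either direction | Favourable direction only |
|---|---|---|
| 0 | 14.3% | 7.3% |
| 0.3 | 13.6% | 6.8% |
| 0.5 | 12.5% | 6.3% |
| 0.7 | 10.9% | 5.5% |
| 0.8 | 9.8% | 4.9% |
| 0.9 | 8.4% | 4.2% |

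The excess over the nominal rate shrinks with correlation but remains at 0.9. If all three outcomes had to be significant, the error would stay below 5%, but the protocol states no such rule.

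**3. What splitting the 0.05 would cost.** With 63 per group and d = 0.5, the expected test statistic is 0.5 × √(63/2) = 2.806.
- At 0.05: Φ(2.806 − 1.960) = 80%.
- At 0.05/3 = 0.0167: Φ(2.806 − 2.394) = **66%**.
- To keep 80% at 0.0167: 2 × (2.394 + 0.842)² / 0.25 = 83.8, so 84 per group and 168 in total before attrition.

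These figures use the two-independent-group formula that reproduces 126, not a stepped-wedge calculation.

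**4. Which score has SD 19.4.** A variable bounded by 1 and 5 has SD at most (5 − 1)/2 = 2. So 19.4 cannot belong to an overall item on the 1–5 scale described in 5.2.2. It could belong to a rescaled item, a domain or a total. The protocol does not say which.

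**The case against.** The strongest reply is that this is an omission, not an error. The rule is one general sentence in a journal article, it does not say that a single significant primary outcome makes the trial positive, and multiplicity is often left to an analysis plan. Part of this stands: the inflation depends on an 'any one' reading that the text does not spell out. But the sentence sets 0.05 for differences in general, the sample size is built on the same 0.05, and no 'all three' rule appears. Powering only one of several primary outcomes is common and would not be a fault on its own.

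Four stronger readings may tempt a reader, and the document does not support them.
- **Eight primary tests, about 34% (1 − 0.95⁸).** This counts all six WHOQoL-Bref scores as primary. The label 'Global' and the secondary place of the physical health subscale speak against it. The defect is an undefined score, not a plan to test six.
- **The powered score is not the global score.** SD 19.4 rules out only a raw 1–5 item. A rescaled item or a total remains possible.
- **Within-group tests add uncontrolled primary tests (six tests, 26.5% if independent).** Section 2.1 has each participant serve as their own control, so 'within' may mean the control-period versus intervention-period contrast. The wording is ambiguous rather than plainly wrong.
- **Session-level mood, pulse and blood pressure add to the primary error.** They are in neither the primary nor the secondary list, so they cannot.

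It is also fair to say that the two-sided figures include false findings of harm. The favourable-direction figures are therefore given beside them.

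**Conclusion.** The point holds in this limited form. Following the plan as written, and letting any one significant primary outcome support a claim, the two-sided family-wise error is 14.3% if the tests are independent and 13.6% to about 8% for assumed correlations of 0.3 to 0.9. For false claims of benefit alone it is about 6–7% up to correlation 0.5, falling to 4.2% at 0.9, against 2.5%. The correlations, the two-sided tests and the 'any one' reading are assumptions.

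Separately, and without any assumption, the primary quality-of-life score is not identified and is not tied to the score with SD 19.4.

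This should be corrected. It does not invalidate the design, and it can be settled without changing the planned sample size if a fixed sequence is chosen.

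**What to change.** 1. In sections 6.1 and 7.1, name the one WHOQoL-Bref score, with its scale, that is both the primary outcome and the basis of the sample size.
2. In the Analysis paragraph, control the error across the three primary outcomes in one of two ways:
   - a fixed sequence declared before the data are seen, with each test at 0.05 only if the one before it is significant. Starting with the powered quality-of-life score keeps 0.05 and the stated power basis for that score. The order is the sponsor's choice; the Introduction stresses psychosocial wellbeing, which is a reason to weigh it openly;
   - Holm's procedure, which needs no order.
3. State that significance for the primary outcomes rests on the Forest Therapy versus control contrast from the mixed model, in line with the hypothesis in section 1.2. Report uncontrolled pre–post changes descriptively with intervals.

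Cost: wording, plus one real trade-off. Under a fixed sequence, later outcomes cannot be confirmed once an earlier one fails; with quality of life first, both psychosocial outcomes depend on it. Under Holm, an outcome faces at worst 0.0167, where power falls from 80% to about 66%, assuming 0.5 SD and 63 per group.

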#### 5.2.3. Social Adjustment and ADLs

The Work and Social Adjustment Scale [59] assesses perceived impairment in functioning in five domains including employment, ADLs, social connection and support, and leisure activities, rated on from 0 (not at all [impaired]) to 8 (very severely [impaired]).

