#### 5.2.4. Loneliness

The UCLA 3-item Loneliness Scale [60] assesses how frequently over the previous two-weeks participants have felt 1. left out, 2. isolated, and 3. lacking companionship, rated from 1 (never) to 4 (frequently).

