#### 5.2.9. Mood

The Profile of Mood States-Adolescents [64], validated in adults [65], assesses current mood across 6 sub-components including anger, confusion, depression, fatigue, tension, and vigour. Twenty-four items are rated based on the extent to which participants are experiencing them “right now”, rated 0 (not at all) to 4 (extremely).

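### The missing-item rule sets one limit as a percentage and the other as a count, leaves exactly 20% unassigned, and fills items across domains on multi-domain tools

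*Protocol article*

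**What the plan says.** The rule is two adjacent sentences in the Analysis section of the protocol article (under 7. Statistical Analysis): "Assessment tools missing <20% responses will be imputed with participant tool mean", followed by "Tools with >20 missing responses will be excluded". No separate rule is given for domains or subscales.

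The tools it governs are described in section 5.2 and ranked in section 6:

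- Social adjustment is primary (section 6.1: "Social Adjustment—Work and Social Adjustment Scale"). Section 5.2.3 says the scale "assesses perceived impairment in functioning in five domains". It gives no item count and names four of the five domains, employment among them.
- Loneliness is primary and is measured by "The UCLA 3-item Loneliness Scale" (section 5.2.4).
- The WHOQoL-Bref is primary as global quality of life. Section 5.2.2 describes two overall items and four domains, and section 6.2.3 makes the "Physical Health Subscale of WHO-QoL-Bref" a secondary outcome in its own right.
- The mood tool has 24 items in six sub-components: "anger, confusion, depression, fatigue, tension, and vigour" (section 5.2.9). It is not listed among the outcomes in section 6.

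**The concern.** Two limits meant to divide the same scale should share a unit and meet at a boundary. Here they do neither. As printed, a short questionnaire with many blanks is neither imputed nor excluded. With a % sign restored, the boundary value itself still belongs to neither sentence, and on a five-item scale that value is the smallest amount of missingness possible.

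The imputation source is a second, independent problem. A mean over the whole tool suits a tool with a single score. Where a domain is scored and reported separately, it replaces a missing item with a value drawn partly from different constructs.

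Whoever scores the data would have to invent a rule for forms on a primary outcome. Imputing, prorating or dropping the score give different analysed data. Section 9.1 states that participants and assessment staff are not blinded, so a rule chosen once data are visible is open to challenge.

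**Working it through.** **Step 1. Apply the rule to each tool.** For m missing items of k, impute if m/k < 0.20. Exclude if m > 20 (as printed) or if m/k > 0.20 (if a % sign was dropped). Any other m has no rule. Item counts come from sections 5.2.3 to 5.2.7 and 5.2.9. The 9 for depression is read from the tool's name, and the 5 for social adjustment assumes one item per domain.

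| Tool | k | Imputed | Excluded, as printed | No rule, as printed | Excluded, if >20% | No rule, if >20% |
|---|---|---|---|---|---|---|
| Loneliness (primary) | 3 | none | none | 1–3 | 1–3 | none |
| Health confidence | 4 | none | none | 1–4 | 1–4 | none |
| Social adjustment (primary) | 5 | none | none | 1–5 | 2–5 | **1** |
| Anxiety | 7 | 1 | none | 2–7 | 2–7 | none |
| Depression | 9 | 1 | none | 2–9 | 2–9 | none |
| Mood | 24 | 1–4 | 21–24 | 5–20 | 5–24 | none |

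The deciding fractions are 1/3 = 33%, 1/4 = 25%, 1/5 = 20.0%, 2/7 = 29% and 2/9 = 22%. The article does not give the WHOQoL-Bref item total. If 26 is assumed, 1–5 missing are imputed, 6–20 have no rule as printed, and 21–26 are excluded. The conclusion does not rest on that figure.

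**Step 2. Test the social-adjustment assumption.** With r items in each of five domains, k = 5r, and r missing items is r/5r = exactly 20%. The equality gap is therefore present for any equal number of items per domain. With r = 1 it is a single missing item.

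**Step 3. Look at what a tool mean does on a multi-domain tool.** Take the mood tool with four items per sub-component (24/6, equal sizes assumed). Suppose vigour items average v, the other 20 items average n, and one vigour item is missing. The imputed value is (20n + 3v)/23, which differs from the participant's own vigour mean by 20(v − n)/23 = 0.87(v − n).

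- With v = n there is no difference.
- With v − n = 1 the shortfall is 0.87.
- With illustrative scores v = 3 and n = 0.5, the imputed value is (10 + 9)/23 = 0.83, not 3. The vigour total becomes 9.83, not 12.

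These scores are invented to show the mechanism and are not taken from the document. For the WHOQoL-Bref physical health subscale the mechanism is the same: a missing physical item is filled partly from social, psychological and environment items. The article gives no domain means, so no size or direction can be computed.

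**Step 4. See where the two problems overlap.** No number of missing items on the loneliness or social-adjustment scale falls below 20%, so neither is ever imputed. The tool-mean problem does not touch those two primary outcomes.

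**The case against.** The strongest reply is that this is a typographical slip. The sentences are adjacent and use the same number, so 'more than 20%' is the natural complement of 'less than 20%'. That is probably right. On that reading the loneliness, health-confidence, depression and anxiety scales all have a clear rule, and what remains is the equality case. A reader might infer from the printed text that two of the three primary scales can never be excluded. That is true only of the literal wording and should not be taken as the trial's intention.

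A reader might also infer that the employment item will be blank on a large share of forms. The document gives neither an employment rate nor a skip rate. Link Workers conduct assessments 1 to 5 (section 5), which makes casual blanks less likely. An item that does not apply is also a different matter from one that was missed. No number of affected forms can be supported.

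A third inference would be that imputed domain scores, including the physical health subscale, are materially wrong. The document supports only that the fill-in value comes partly from other domains. The mood example shows a clear direction because vigour runs opposite to the rest, but mood is not a listed outcome.

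Finally, item-level scoring is often left to a fuller document. That would excuse silence. Here the article states a rule, and the rule as stated has a gap and names the wrong source for domain scores.

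**Conclusion.** The point holds in a limited form. It is certain from the text that the two limits use different units and that exactly 20% is covered by neither. As printed, the exclusion limit is out of reach on five scales, two of them primary. If a % sign was dropped, the gap on the tools with known or assumed counts narrows to one missing item of five on the Work and Social Adjustment Scale, given one item per domain.

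The tool-mean instruction is unsuitable wherever a domain is scored separately. That covers one listed secondary outcome (physical health) and the mood sub-components. The size of any effect on the WHOQoL-Bref is unknown. The sample size and the choice of mixed model are unaffected. This should be corrected because it reaches a primary outcome and costs almost nothing to repair, but it does not threaten the trial's design.

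**What to change.** Use percent in both sentences, assign equality, and tie imputation to the score being formed. For example:

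> If at most 20% of a tool's items are missing, impute with the participant's mean of the answered items in the same domain or subscale (the whole tool only for single-score tools), after aligning item direction. If more than 20% are missing, or a subscale has no answered items, that score is missing at that assessment and the participant stays in the mixed model.

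This imputes 1 of 5 social-adjustment items and leaves the loneliness score missing when 1 of 3 items is blank. The limit stays at tool level on purpose: a 20% limit within each subscale would set a four-item sub-component to missing after one blank (1/4 = 25%). The trade-off is that a small subscale may be completed from few answers. For example, three blanks of 24 mood items is 12.5%, yet they could all fall in one sub-component.

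State separately how a not-applicable employment item on the Work and Social Adjustment Scale is scored, since that is not the same as a missed answer.

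The cost is a few sentences and a small change to the scoring script, with no new data.
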